#### Procedure

We will start with recruitment of novice therapists (see below for details). Followed by a general training for all therapists in the basics of the treatment programs and routines. Here therapists learn to use the general therapist manual. After the general training a suitability testing of all therapists is performed to ensure that they have an adequate level of expertise in ICBT. After training therapists are randomized, 1:1 ratio, to either ICBT with DST or ICBT TRAD. The randomization is handled by an independent party (Karolinska Trial Alliance (KTA)) and will be on the therapist level. Separate, specific training of the two experimental groups, where both groups will be informed that they are in the “active” group. One group will be trained in how to use the DST and the other group will receive further training in the clinical routines and treatment structure (they will again be informed that this specific treatment structure and manual is what is being evaluated). Both groups receive a specific therapist manual adapted for DST or TRAD.

Recruitment and assessment of patients is done parallel to therapist recruitment and training. Randomization of patients is done to the two treatment arms, 1:1 ratio. After randomization patients receive 12 weeks of guided ICBT with a DST or guided ICBT TRAD. Patients answer online questionnaires at screening, pre-treatment, weekly measures during treatment, post-treatment and at follow-up assessment.

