#### Participants and recruitment

Both therapists and patients are participants in this trial. The trial will consist of 10-40 novice therapists, primarily students in the final year of the 5-year clinical psychologist program, with basic education in CBT but little or no experience of ICBT. Each will treat 5-25 patients (total patient n=250 - 700).

The therapists will be recruited nationally in Sweden from different clinical psychologist programs thru advertising and contacts with key persons at these universities. If necessary additional therapists will be recruited among students who are finishing the two-year basic training program in CBT, plus among intern psychologists (‘PTP-psykolog’) at the psychiatric clinic at Psykiatri Sydväst in Stockholm. The patients will be recruited through the Internet Psychiatry Clinic routine intake plus through advertising on the web, for example on [www.studie.nu](http://www.studie.nu), and in traditional media.

A large number of ICBT studies have successfully used therapists with this level of competence. None of the therapists (or patients) will be aware of the randomization. Therapists are informed they will have the opportunity to learn ICBT within the context of a clinical trial evaluating slightly different versions of ICBT, and receive a diploma and in some cases a small monetary reimbursement or the possibility to take the course and treat the ICBT patients during office hours.

The patients in this setting will also be recruited nationally and assessed via internet and structured, diagnostic video- or telephone interviews according to well established procedures from previous ICBT-trials. Its content will mimic the assessment at the Internet Psychiatry Clinic.

*Inclusion criteria:*

- 18 years or older.
- Social anxiety, panic disorder or depression diagnosis.
- Stable or no antidepressant medication for at least 2 months.
- No diseases, disorders, or substance abuse that required other, immediate attention (e.g., severe depression or suicidality).
- Available time for treatment and acceptance of its format.
- Proficient in Swedish.
- No ongoing CBT.

*Exclusion criteria:*

- Not available for assessment and diagnostic telephone interview.
- Will not be in Sweden during the treatment period.
- Not able to receive text messages on a Swedish mobile phone.
- Not proficient in Swedish.
- No access to computer and internet.
- Not able to set aside about one hour a day to work on treatment.

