#### *Statistical Analyses*

Primary analyses will be performed according to the intent-to-treat principle with Longitudinal Multilevel Modelling ('Mixed Models') or GEE including baseline covariates to control for non-random missingness. The power analysis is based on the primary hypothesis concerning differences in symptom reduction between DST and TRAD for patients being predicted to fail. Our previous proof-of-concept trial (13) shows that patients that during week four are predicted to fail and then receives enhanced ICBT increase their outcome (Cohen's  $d=0.53$ ) compared to those predicted to fail that stays on standard ICBT. To be conservative, we now estimate the effect the decision support tool to be  $d=0.40$ , which with a power of 80% and an data attrition of 20% would require 250 patients. Mainly because some secondary hypotheses are assumed to need more power and partly because the estimated effect is somewhat unsure and the design with randomization on the therapist level might can decrease power further (15), we will perform an interim, renewed power analysis after 250 patients have finished treatment. Depending on this analysis we can, if needed, include up to a total of 700 patients.

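### The stated 80% power with 250 patients makes no allowance for randomising therapists, and the planned extension is counted in patients only

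*Protocol*

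**What the plan says.** The Procedure section puts randomisation at the therapist level: "After training therapists are randomized, 1:1 ratio, to either ICBT with DST or ICBT TRAD". Patients are also randomised 1:1 to the same two arms, but each therapist works in one arm only. Under Participants and recruitment, "The trial will consist of 10-40 novice therapists", and "Each will treat 5-25 patients (total patient n=250 - 700" in total. The minimum is therefore 5 therapists per arm.

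The Statistical Analyses section bases the sample size on d = 0.40 for symptom reduction among patients predicted to fail, "which with a power of 80% and an data attrition of 20% would require 250 patients". It gives no ICC and no design effect. It then remarks that "the design with randomization on the therapist level might can decrease power further", and plans a renewed power analysis once 250 patients have finished treatment, with a ceiling of 700 patients. The primary analysis is to be a longitudinal multilevel model "or GEE including baseline covariates to control for non-random missingness".

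**The concern.** When therapists are randomised and patients are nested in therapists within arm, differences between therapists go straight into the treatment contrast. Randomising patients to arms as well does not remove this, because no therapist treats in both arms. Two things follow: the variance of the contrast is inflated by the design effect, and the degrees of freedom depend on the number of therapists rather than the number of patients.

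The protocol names the loss of power but puts no size on it. Its remedy is stated in patients, although the number of therapists limits both the precision and, through the ceiling of 25 patients each, how far recruitment can go. At stake is a primary hypothesis tested at well below the advertised 80% power, with the shortfall examined only after 250 patients have finished. By then the first therapists have long been recruited, trained and randomised.

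**Working it through.** **Inputs from the protocol.** d = 0.40, 80% power, 20% attrition and 250 patients (Statistical Analyses); therapists randomised 1:1 (Procedure); 10 to 40 therapists with 5 to 25 patients each (Participants and recruitment).

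**Assumptions.** Alpha is not stated. A two-sided 5% level is used because it reproduces the 250; a one-sided 5% level would give 195. The ICC is not stated, so 0.01 to 0.10 is shown. Clusters are of equal size. All 250 patients are granted to the primary analysis, although the primary hypothesis covers only those predicted to fail; this favours the plan.

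**Step 1: reproduce the 250.** By the normal formula, n per arm = 2 × (1.96 + 0.84)² / 0.40² ≈ 98.1, so 99 per arm and 198 in total; 198 / 0.8 ≈ 248. Rounding the t-test requirement up to 100 per arm gives 200 / 0.8 = 250. Both use a design effect of 1.

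**Step 2: add the therapist level.** 250 × 0.8 = 200 patients analysed. With K therapists:
- m = 200 / K analysed patients per therapist
- DE = 1 + (m − 1) × ICC
- non-centrality = 0.40 × √(100 / (2 × DE))
- power from the non-central t on K − 2 degrees of freedom

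Example, K = 10 and ICC 0.05: m = 20; DE = 1 + 19 × 0.05 = 1.95; non-centrality = 0.40 × √(100 / 3.90) = 2.03; critical t on 8 df = 2.31; power 43%.

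| Therapists | m | ICC 0.01 | ICC 0.05 | ICC 0.10 |
|---|---|---|---|---|
| 10 | 20 | 62% | 43% | 31% |
| 20 | 10 | 73% | 60% | 49% |
| 40 | 5 | 77% | 71% | 64% |

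Even with ICC = 0, 10 therapists give 70%, because the test rests on 8 df. No cell reaches 80%.

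**Step 3: the extension.** At 25 patients each, 10 therapists can treat at most 10 × 25 = 250 patients, and 700 patients need at least 700 / 25 = 28 therapists. On the same basis as Step 2:
- 28 therapists, 700 patients (560 analysed, m = 20): 90% at ICC 0.05 and 76% at ICC 0.10.
- 40 therapists, 700 patients (m = 14): 95% and 86%.
- 20 therapists, 500 patients (400 analysed, m = 20): 77% at ICC 0.05, up from 60% with 250 patients.

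**Step 4: conditional check on GEE.** This applies only if GEE is chosen, clustered on therapist, with an uncorrected sandwich variance and a z-test. In simulation (20,000 trials per setting, 200 analysed, nominal 5%), the type I error is about 12% with 10 therapists, 8% with 20 and 6% with 40, nearly the same across the ICC range. A corrected variance with a t reference on therapist degrees of freedom gives about 5%. Direct exchangeable GEE fits (1,000 trials, 10 therapists, ICC 0.05) gave 12.5% uncorrected and 6.1% with a bias-reduced covariance.

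**The case against.** The strongest reply is that the protocol does not hide the problem. It names the loss from therapist-level randomisation, cites a simulation study on ignoring therapist effects, and schedules a renewed power analysis with room to grow to 700. That stands: the 80% is a provisional figure with a caveat. But the caveat has no size attached, and no minimum number of therapists accompanies it.

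A second reply is that the ICC drives the answer and is unknown. This also stands. At ICC 0.01 with 40 therapists power is 77%, a small loss. The protocol, however, permits anything from 10 to 40 therapists, and at the lower end the shortfall is large for every ICC shown.

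A reader might go further than the document allows in three ways:
- **That the GEE option makes the primary test invalid.** Multilevel models are named first. Nothing says that GEE would be uncorrected or that therapist would be left out. Random effects and small-sample corrections commonly belong to the SAP, which is not shown, so their absence here is not an error.
- **That extra patients cannot help.** With 20 therapists at ICC 0.05, going from 250 to 500 patients raises power from 60% to 77%. The limit binds near the floor, where the ceiling of 25 patients per therapist already stops 10 therapists at 250.
- **That 700 patients would still be too few.** With all patients counted, 28 therapists and 700 patients give 90% at ICC 0.05. A lower figure requires a share of patients predicted to fail, which the protocol does not give and which is a separate question.

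**Conclusion.** The point holds as a fault in the stated power and in how the extension is expressed. With 250 patients, 80% power is not reached at 10, 20 or 40 therapists under the assumed ICCs: the range is 31% to 62% at the floor of 10 and 64% to 77% at the ceiling of 40. These figures rest on two-sided 5% alpha, ICC 0.01 to 0.10, equal clusters, K − 2 degrees of freedom, and all 250 patients counting towards the primary analysis. The route to 700 can restore power at moderate ICCs, but it needs at least 28 therapists, which the Statistical Analyses section does not say. The type I error under GEE is a conditional caution only; it matters mainly at 10 to 20 therapists and is small at 40.

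**What to change.** 1. Restate the power at 250 patients with the design effect 1 + (m − 1) × ICC, where m is the number of patients per therapist in the primary analysis, using therapist-based degrees of freedom and a stated ICC range. Use the same calculation in the renewed power analysis.
2. State a minimum number of therapists within the planned 10 to 40. Express the extension in therapists as well as patients, noting that 10 therapists stop at 250 patients and that 700 needs at least 28.
3. As a conditional point, add one sentence that whichever primary model is used will account for therapist, with small-sample degrees of freedom for a mixed model, or a bias-corrected sandwich if GEE is chosen. If the SAP already says this, a cross-reference is enough.

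The cost is wording, a lower stated power at 250 patients and slightly wider confidence intervals. The therapist minimum stays inside the planned range.
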